### Plans to give access to the full protocol, participant-level data, and statistical code {31c}

Data sharing statement is no later than 3 years after the collection of the 1-year post-randomization interviews. We will deliver a completely identified dataset to an appropriate data archive for sharing purposes. The datasets analyzed during the current study are available from the corresponding author on reasonable request.

## Oversight and monitoring

### Composition of the coordinating center and trial steering committee {5d}

#### Organizational structure and responsibilities

##### First author and the second one (the supervisor)

Preparation of protocol and revisions.Application procedures for obtaining approval of the Research Ethics Committee.Implementation of modifications required for the research registration and obtain the required approval from the Ethics Committee of Scientific Research.Publication of study reports.The supervisor will be responsible for reviewing the progress of the study and if necessary agreeing changes to the protocol.

##### Trial steering committee

The committee will be formed by the Scientific Research Department of Tishreen University. Tishreen University research supervisor will be nominated as a coordinator. The steering committee should monitor trial progress and conduct and advise on scientific credibility. It will consider and act, as appropriate, upon the recommendations of the Ethics of Scientific Research Committee at Tishreen University and ultimately carries the responsibility for deciding whether a trial needs to be stopped on grounds of safety or efficacy. It will be observing the recruitment of participants with liaising with the principal researcher and reviewing the progress of the study and if necessary agreeing changes to the protocol brochure to facilitate the smooth running of the study. The steering committee will meet once every 2 weeks to discuss the reports and the monitoring process. There will be no Stakeholder and Public Involvement Group.

### Composition of the data monitoring committee, its role and reporting structure {21a}

There is no need for a formal data monitoring committee because of the short duration of the training program and the known minimal risks.

### Adverse event reporting and harms {22}

The adverse event will be defined as any serious injury that occurred in a subject without regard to the possibility of a causal relationship. Adverse events will be collected after the subject has provided consent and enrolled in the study.

If a subject experiences an adverse event after the informed consent document is signed (entry) but the subject has not started to receive study intervention, the event will be reported as not related to study drug. If training is discontinued as a result of an adverse event, study personnel will document the circumstances and data leading to discontinuation of the exercise.

Investigators will determine the relatedness of an event to study protocol based on the physical health situation for the subject before beginning the training program and the temporal relationship to the study training.

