### Strategies to improve adherence to interventions {11c}

The adherence reminder sessions will take place 15 min before every training session. This session will include the following:
The importance of following a training program for general health.Instructions about how to practice carefully and how to avoid physical collision between participants, especially in competitions or games.The importance of adherence in order to develop the performance of the body, and the negative effects of absence from any training session.Instructions about the purpose of the study and the training plan.Instructions the importance of informing the coach about any injury or physical pain.Participants will have an opportunity to ask questions throughout the training program at any time.

Before the starting of every single month of the training program, there will be a special recreational trip in order to increase the motivation and commitment of participants.

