#### Isokinetic muscular power and work test

The power of knee extensor and flexor muscles will be measured in a sitting position using isokinetic dynamometers (Genu3 Easytech, Florence, Italy). After warm-up exercises, patients perform 4 maximal concentric strokes at an angular speed of 90° per second (knee extension flexion; ROM, 90–0°). Isokinetic tests will be performed when patients have no pain or swelling with ROM more than 120° of flexion with full extension. To ensure maximal effort, 3 to 4 training sessions are allowed before performing the test.

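### The adverse event definition admits only serious injuries, and a rule worded for a drug trial labels events before training as unrelated, although maximal baseline testing falls in that period

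*Protocol article*

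**What the plan says.** All the governing text is in the section Adverse event reporting and harms {22}, which makes four statements.

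- Definition: "The adverse event will be defined as any serious injury that occurred in a subject without regard to the possibility of a causal relationship".
- Start of collection: "Adverse events will be collected after the subject has provided consent and enrolled in the study".
- Automatic rule: if the event comes after the consent form is signed "but the subject has not started to receive study intervention", then "the event will be reported as not related to study drug".
- Case-by-case rule: "Investigators will determine the relatedness of an event to study protocol based on the physical health situation for the subject" before training, together with the timing of the event relative to the training.

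Two other places bear on the point. Strategies to improve adherence to interventions {11c} lists, among the topics of the reminder session, "Instructions the importance of informing the coach about any injury or physical pain". The section on the data monitoring committee {21a} explains that none is needed "because of the short duration of the training program and the known minimal risks".

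**The concern.** The definition is wide on causality and narrow on everything else. An event must be an injury, and the injury must be serious. A strain or contusion does not qualify, and neither does chest pain, syncope or an arrhythmia. The trial puts untrained men of 50 to 60 through 24 sessions of football or running. The article treats injury as a live risk: it builds injury-prevention exercises into each session because of the men's age, and it instructs them on avoiding collisions. Any later statement about the safety of football against running would rest on serious injuries alone.

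The automatic rule raises a different problem. It assumes that nothing the study does before the first session can harm a participant. That assumption comes naturally in a drug trial with harmless screening visits. Here the baseline visits include maximal-effort tests, which are study procedures.

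**Working it through.** There is no figure in the plan to reproduce. The check sets the passages against each other and against the dates.

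**1. Does any other text widen the definition?** No.
- Criteria for discontinuing {11b} refers to serious physical injury or to being unable to continue for other reasons. It governs removal from the programme, not recording.
- Strategies to improve adherence {11c} asks men to tell the coach about any injury or pain, but does not link those reports to adverse events.
- Provisions for post-trial care {30} promises treatment for injuries in sessions, but creates no record of harms.

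**2. What lies in the window of the automatic rule?** Table 4 puts consent at enrolment, the tests at baseline, and training from week 1. The dates come from Outcomes {12} and Participant timeline {13}.
- First baseline test 1 March 2020, training from 15 April 2020: 30 + 15 = 45 days before training.
- Last baseline test 20 March 2020: 11 + 15 = 26 days before training.
- Isokinetic test-retest session two weeks before the intervention, so about 1 April 2020.

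All of these fall inside the window. The tests concerned are demanding. In the isokinetic test "patients perform 4 maximal concentric strokes at an angular speed of 90° per second". The vertical jump asks for three jumps as high as possible. The Yo-Yo run continues until the second consecutive failure.

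**3. What happens to each kind of event as written?**

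| Event | Consent to first session (includes baseline tests) | From first session |
|---|---|---|
| Serious injury | Collected, labelled unrelated by rule | Collected, relatedness judged |
| Non-serious injury | Not an adverse event | Not an adverse event |
| Non-injury medical event | Not an adverse event | Not an adverse event |

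**4. Do the two relatedness rules agree?** No. The automatic rule asks about a drug and settles the answer in advance. The case-by-case rule asks about the study protocol, which would include testing. Yet the only timing it considers is relative to training, so a test-related injury fits neither rule.

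**5. Can the share missed be sized?** Not from the article. With assumed values:
- Exposure per arm: 30 men × 24 sessions × 1 h = 720 h.
- Assumed 3 to 10 injuries of any grade per 1000 h: 720 × 3/1000 = 2.2 to 720 × 10/1000 = 7.2 injuries per arm.
- Assumed 10% to 20% serious: 2.2 × 0.10 = 0.2 to 7.2 × 0.20 = 1.4 recorded per arm.

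The share of injuries missed here is simply one minus the assumed serious share, 80% to 90%. The calculation returns its own input, so it illustrates the point and is no evidence for it.

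**The case against.** **The rule may be right on its own terms.** An event before any training cannot be caused by training. If the drug is read as a slip for the intervention, the label is true, and relatedness to the protocol is judged separately in the next paragraph. This is a fair reading, and it is why the criticism is that the two rules need reconciling. It does not close the gap, because that second judgement also looks only at timing relative to training.

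**Other safeguards exist.** Events that end participation would show up as discontinuations. The investigator undertakes to provide treatment for injuries in sessions. The steering committee meets every two weeks and is responsible for stopping on safety grounds. All true, but none of these changes what counts as an adverse event. The absence of a data monitoring committee is explained and is not part of this point.

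**A condensed article leaves detail out.** That covers the layout of a session log. It does not cover a definition that the article states in full and states too narrowly.

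**Stronger readings that the documents do not support:**
- *Most harms will be missed.* The article gives no event rates and no split by seriousness.
- *The plan would hide a clear difference in injuries between the arms.* No such difference is shown. Comparing injuries is not a stated objective, and only 35 of the 60 minutes differ between arms (Table 2). That is 30 × 24 × 35/60 = 420 h per arm, or 1.3 to 4.2 injuries at the assumed rates. With so few, even full recording would rarely separate the arms.
- *Baseline-test injuries go uncollected.* Concealment mechanism {16b} could be read as placing recruitment after the baseline measurements. However, the harms section equates entry with signing consent, and Table 4 puts enrolment before baseline. Serious ones are therefore collected.
- *The automatic rule biases the comparison.* The randomization code is released only after all baseline measurements, so these tests precede allocation. The article does not say whether the test-retest session also does, but the rule is mechanical and would treat both arms alike.

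**Conclusion.** The concern holds in two parts.

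First, by its stated definition the plan excludes every non-serious injury and every non-injury medical event from the harms record, in both arms and throughout the trial. This needs no assumption. Its numerical size is unknown. The consequence is that any safety comparison of football with running would cover serious injuries only.

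Second, the automatic rule names a drug that does not exist, covers the whole baseline testing period, and conflicts with the relatedness sentence in the same section. Serious injuries caused by study testing could be classed as unrelated. That may understate the harms of study procedures, without distorting the contrast between arms.

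No primary or secondary outcome analysis is affected. The change is worth making because it is cheap and because harms left unrecorded cannot be recovered reliably afterwards.

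**What to change.** In Adverse event reporting and harms {22}:

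1. Define an adverse event as any untoward medical occurrence from consent to the post-intervention test, whether or not it is an injury, and classify each by seriousness.
2. Record events at each training session and each test visit, using among other sources the reports that participants are already asked to give the coach. Report them by arm, with events before allocation listed separately.
3. Delete the rule that refers to a drug. Reconcile it with the relatedness sentence, so that one judgement covers study testing as well as training and considers timing relative to both.

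The cost is a few sentences of protocol text and a short entry per session or visit. The downside is slightly more recording and a safety table that will look less favourable.

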### Frequency and plans for auditing trial conduct {23}

Project Management Group will meet 4 days a week, before every single training. The Trial Steering Group and the Ethics Committee will meet two times per month to review conduct throughout the trial period.

### Plans for communicating important protocol amendments to relevant parties (e.g., trial participants, ethical committees) {25}

Any modification of the research procedures including changes of study objectives, study design, participant population, sample sizes, study procedures, or significant administrative aspects will lead to a change in the study protocol.

It will be under the supervision of the responsible professor and approved by the Ethics Committee of Tishreen University prior to implementation.

## Dissemination plans {31a}

This research is a part of a Ph.D. thesis, and the publishing rights are owned by the authors. The results will be presented several times to the supervisor professor and resident committee at German Sport University. Additional dissemination will occur through presentations at conferences, such as science education conferences, regionally and nationally, and through articles published in peer-reviewed journals.

The first author is delegated from Tishreen University to obtain a doctorate degree, and therefore, the university will be responsible only for providing the facilities and logistical support to complete the research.

The first author is a Ph.D candidate at the German Sport University Cologne, and all the results and researches related to the trial will only be published through it. The recruitment has been ended on 31 March.

## Discussion

Previous research has demonstrated that practicing small-sided recreational soccer games is an effective health-promoting activity for both untrained men and women. In untrained premenopausal women, thirty-seven participants were randomized to two training groups—football and running—training 1 h with equal average heart rates for 16 weeks (twice a week). The results show that there are effects on both left ventricular systolic and diastolic function and the training-induced cardiac adaptations appeared to be more consistent after football training compared with running [7]. In the same way, fifty healthy women were matched and randomized to a football (*n* = 25) or a running (RG, *n* = 25) group and compared with a control group with no physical training. After 16 weeks, resting heart rate was lowered, maximal oxygen uptake was elevated, and total fat mass decreased [32].

For untrained men, Krustrup et al. [30] have shown that recreational soccer training, organized as small-sided drills, has significant beneficial effects on health profile and physical capacity. In a study of some aspects, it is superior to frequent moderate-intensity running training, after training performed for 1 h (two or three times per week) for 12 weeks, at an average heart rate of 82% and 82% (1%) of HR (max) for 36 healthy men in football group and running group. Recreational football stimulates both aerobic and anaerobic energy turnover and is an effective type of training leading to significant cardiovascular and muscular adaptations as well as performance enhancements throughout a 12-week training period [31]. Moreover, positive adaptations in cardiovascular fitness obtained over 12 weeks of regular recreational football training with further development in musculoskeletal fitness [43]. Also, Andersen et al. [8] have investigated whether football has favorable effects in the treatment of mild-to-moderate arterial hypertension. The study included 25 untrained males aged 31–54 years. They were randomized to a football training group and a control group for 3 months. The results show that football as a treatment for hypertension can be an attractive non-pharmacological supplement to the treatment of mild-to-moderate arterial hypertension.

On the other hand, Timmins et al. [51] studied the architectural adaptation of the long head of the biceps femoris after concentric or eccentric strength training in the adaptation period of training and detraining. The results show that short-term strength training can contribute to the architectural change in the long head of the biceps femoris. Narici et al. [40] examined the impact of aging on muscle architecture of the medial gastrocnemius in 14 young and 16 elderly physically active people, who have had the same height, body weight, and physical activity regimen. Young people varied by age from 27 to 42 years and elderly people were 70–81 years old. Anatomical CSA and the volume of the medial gastrocnemius muscle were measured by computed tomography, and the length of the beams and PA were measured by ultrasound. Anatomical CSA and the amount of muscle in the elderly amounted to 19.1%, while in the young participants 25.4%. FL and PA also were smaller in the elderly group (10.2 and 13.2%, respectively). Another study investigated whether increased tendon-aponeurosis stiffness and contractile strength of the triceps surae muscle-tendon units induced by resistance training would affect running economy. This study was conducted on an exercise group (*n* = 13) which performed a 14-week exercise program. The results show after resistant training intervention an increase in maximum plantarflexion muscle strength (∼ 7%) and an increase in triceps surae tendon-aponeurosis stiffness (∼ 16%) [3].

Another study [10] investigated the effects of sports training on muscle architecture; 8 female and 15 male athletes performed 4 weeks of sprint, jump, and resistance training in addition to their sports training (standardization) before adopting one of three different sports programs. Muscle size, fascicle angle, and FL of the VL and RF muscles (using ultrasound procedures) as well as 20-m sprint run, vertical jump, and strength performance changes were examined. Significant muscle size and architectural adaptations can occur in concurrently training athletes in response to a 5-week training program, and these adaptations were possibly associated with the force and velocity characteristics of the training exercises. Angelik et al. [5] have studied the rate of force development (RFD) and muscle architecture early adaptations in response to training with fast- or slow-velocity eccentric squats. Eighteen young novice participants followed 6 weeks (two sessions/week) of either fast-velocity (Fast) or slow-velocity (Slow) squat eccentric-only training. The results of this study suggest that fast eccentric resistance training may be more appropriate for increases in rapid force production compared to slow eccentric resistance training, and this may be partly due to increases in muscle FL induced by fast eccentric training. Moreover, the main muscle architecture parameters, which were assessed through muscle ultrasound, had demonstrated some degree of alteration in the quadriceps femoris and gastrocnemius medialis, and each of these parameters may be theoretically useful for detecting the loss of muscle mass and functionality in geriatric patients [50].

However, so far, almost no studies compared the effects of football and running training interventions on the age-related decline of muscle strength and structure. This is the first study that aims at investigating the differential effects of football and running training response on muscle architecture, patella tendon properties, and thigh muscles. The proposed study should benefit participants’ physical, psychological, and social dimensions. It is assumed that running and football training not only may result in the improvement of the aerobic capacity and systemic arterial blood pressure reductions, but also can improve the functional parameters, including increased explosive power strength, balance, agility, and functional capacity. As our primary hypothesis, we expect moderate differences between both groups in muscle architecture CSA, FL, MT, PA, knee ROM, passive resistive torque, work, power, and tendon length and thickness as football entails are broader and multimodal muscular stimulus compared to aerobic training alone. These may lead to overall decrease in obesity risk and stress, and it could also prevent heart diseases, maintain muscle mass, and reduce the risk of depression. Moreover, the training programs may enhance muscle architecture and tendon thickness that causes a perceptible decrease in the probability of dynapenia and sarcopenia in the future.

## Trial status

The recruitment will start on 1 February 2020 and end on 15 March 2020.

Protocol version Number: 05.

## Abbreviations

VM: Vastus medialis
VL: Vastus lateralis
PA: Pennation angle
PT: Patella tendon
ROM: Range of motion
FL: Fascicle length
MT: Muscle thickness
CSA: Cross-section area
ML: Muscle length
HR: Heart rate
VO2 max: Maximal oxygen uptake
SPIRIT: Standard Protocol Items: Recommendations for Interventional Trials
